**Primary Endpoint:**

1. Recommended dose (RD) of evorpaccept (ALX148) in combination with cetuximab and pembrolizumab
2. Objective response rate (ORR, per RECIST v1.1)

**Secondary Endpoints:**

1. Disease control rate (DCR, per RECIST v1.1)
2. Duration of response (DOR, per RECIST v1.1)
3. Progression-free survival (PFS, per RECIST v1.1)
4. Overall survival (OS)
5. First-cycle dose-limiting toxicities (DLTs) in stage 1
6. Safety and tolerability defined and graded according to the NCI CTCAE v5.0

**Exploratory endpoints:**

1. Objective response rate (ORR, per iRECIST), disease-control rate (DCR, per iRECIST), duration of response (DOR, per iRECIST), and progression-free survival (PFS, per iRECIST)
2. Change in pre- and post-treatment levels and activation of immune cells in the peripheral blood and tumor microenvironment
3. Change in pre- and post-treatment mRNA expression in a panel of immune-related genes in tumor tissues
4. Objective response rate (by RECIST v1.1 and iRECIST) according to change in pre- and post-treatment levels and activation of immune cell in the peripheral blood and tumor microenvironment
5. Objective response rate (by RECIST v1.1 and iRECIST) according to pre-treatment PD-L1, EGFR, and CD47 tumor expression by immunohistochemistry

6. Objective response rate (by RECIST v1.1 and iRECIST) according to tumor mutational burden (TMB)

## 4 STUDY DESIGN

### 4.1 OVERALL DESIGN

#### 4.1.1 STUDY OVERVIEW

This is an open-label, multi-center, single-arm phase II clinical trial (with safety run-in) evaluating the combination of evorpacept (ALX148), cetuximab, and pembrolizumab in patients with metastatic microsatellite stable colorectal cancer who have progressed on at least 2 lines of systemic therapy. A patient who progressed on a single line of therapy including a fluoropyrimidine, oxaliplatin, and irinotecan for unresectable metastatic colorectal adenocarcinoma (e.g., FOLFIRINOX or FOLFOXIRI) is eligible. Patients will be eligible regardless of tumor sidedness or RAS/BRAF status, as the desired mechanism of action of cetuximab is to generate ADCP in synergy with evorpacept (ALX148). However, there is one exception. Patients with left-sided (at or distal to the splenic flexure) RAS/BRAF WT mCRC who are EGFR inhibitor naïve will be excluded. EGFR inhibitor (cetuximab or panitumumab) monotherapy and in combination with chemotherapy has been shown to improve outcomes in patients with left-sided RAS/BRAF WT mCRC (variably ORR, DCR, PFS, and OS). However, patients with RAS/BRAF mutations and/or right-sided tumors respond poorly to EGFR inhibitors. Therefore, patients with left-sided, RAS/BRAF WT mCRC who are EGFR-inhibitor naïve would be expected to benefit from cetuximab alone or in combination with chemotherapy (due to EGFR signaling pathway inhibition) and will be excluded from this study. Baseline tumor EGFR expression will be evaluated as an exploratory endpoint.

There are 2 stages to this study:

1. Stage 1: safety run-in (N = no more than 18 evaluable)
2. Stage 2: dose expansion (N = 42), with two cohorts – Cohort A (N=23, will undergo paired pre- and post-treatment biopsies) and Cohort B (N=19, will not undergo paired biopsies)

**Protocol amendment version 2 (dated December 28, 2022):** The study DSMC will meet after N=12 patients in Stage 2 have been treated for at least one cycle each to review the totality of available safety data; study enrollments and treatments will continue around this review, unless otherwise communicated by the DSMC.

Using a Simon-like 2-stage design, ORR will be determined based on the first 24 evaluable patients (including patients in both Stage 1 and Stage 2). If there are no responses (partial response or complete response as defined in the protocol) in the first 24 evaluable patients, then study enrollment will be stopped for futility. If there is at least one response (partial response or complete response as defined in the protocol) in the first 24 evaluable patients then full study enrollment will proceed as planned. If there are no responses (partial response or complete response as defined in the protocol) in the first 23 evaluable patients then enrollment will be temporarily paused to allow response evaluation of the 24th evaluable patient after up to 15 total weeks (ie 5 total cycles) of study therapy. If the 24th patient has response (partial response or complete response as defined in the protocol) then then full study enrollment will proceed as planned. If the 24th patient does not have a response (partial response or complete response as defined in the protocol) then the study will be stopped for futility. See Section 9.4.2 for statistical considerations.

A subset of patients (Cohort A) will undergo paired pre- and post- (around C3D1) treatment biopsies. See Section 4.1.4 for additional information regarding tumor biopsies.

There will be a 4-week window during which screening can occur. Patients in both the safety run-in and dose expansion stages will continue to receive study therapy until disease progression according to RECIST v1.1 (Appendix 2), unacceptable toxicity, death, patient or physician decision to withdraw, or pregnancy, whichever occurs first. The maximum duration of pembrolizumab is 35 cycles. There is no maximum duration of evorpacept (ALX148) or cetuximab.

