### 1. Dose Levels:

- Evorpaccept (ALX148) dose level (DL) 1: 15 mg/kg weekly; DL -1: 10 mg/kg weekly; DL -2: 5 mg/kg weekly
- Cetuximab DL 1: 250 mg/m^2 weekly; DL -1: 200 mg/m^2 weekly; DL -2: 150 mg/m^2 weekly
- Pembrolizumab DL 1: 200 mg every 3 weeks (no additional dose levels)

2. The desired mechanism of action of cetuximab is to augment phagocytosis via antibody-dependent cellular phagocytosis (ADCP) rather than to modulate the EGFR signaling pathway.

3. No more than 18 evaluable patients will be accrued in Stage 1. A single patient will be treated with evorpacept (ALX148), cetuximab, and pembrolizumab, followed by a 48-hour safety observation period prior to treating the next patient. A 48-hour safety observation period will be required between the start of treatment for patients in Stage 1. Additional patients may be enrolled at lower dose levels if at least 33% of patients experience a first-cycle dose limiting toxicity.
4. If a significant portion of patients in Stage 2 experience AEs meeting dose-limiting toxicity (DLT) criteria as defined in Section 4.1.5, then dose reduction(s) of evorpacept (ALX148) and/or cetuximab for subsequent patients can be considered in discussion with the Investigators and Medical Monitor.
5. A Simon-like 2-stage design will be used. If there are no responses (partial response or complete response) among the first 24 evaluable patients (including patients in both Stage 1 and Stage 2), study enrollment will be stopped for futility. Otherwise, full study enrollment will continue as planned.

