### 8.1 EFFICACY ASSESSMENTS

Baseline tumor assessments should be performed  $\leq 28$  days before Cycle 1 Day 1 and assessed according to RECIST v1.1 and iRECIST (see Appendix 2). The same procedure used to assess disease sites at baseline should be used throughout the study (e.g., the same contrast protocol for CT scans or MRI scans). CT or MRI scans should include chest, abdomen, and pelvic scans; and other areas as clinically indicated. At the investigator's discretion, imaging may be repeated at any time if progressive disease is suspected. Evaluation of tumor response conforming to RECIST v1.1 and iRECIST must be documented every 9 weeks  $\pm 5$  days (no matter where the patient is in the treatment cycle). Patients in both the safety run-in and dose expansion stages will continue to receive study therapy until disease progression according to RECIST v1.1 (Appendix 2), unacceptable toxicity, death, patient or physician decision to withdraw, or pregnancy, whichever occurs first.

In all cohorts, at the time of RECIST v1.1-defined progression (i.e. iUPD), treatment is permitted to continue until the next assessment (at least 4 weeks but no longer than 8 weeks later) if the following criteria are met:

- Patient is clinically stable (An assignment of clinical stability requires that no worsening of performance status has occurred, that no clinically relevant increases in disease-related symptoms such as pain or dyspnea occur that are thought to be associated with disease progression (these symptoms are generally understood to mean a requirement for increased palliative intervention), and that no requirement for intensified management of disease-related symptoms exists, including increased

- analgesia, radiotherapy, or other palliative care.)
- Absence of tumor progression at critical anatomical sites (e.g., leptomeningeal disease) that cannot be managed by protocol-allowed medical interventions
  - Patient and investigator agree to continue treatment
  - Patient signs the Treatment Beyond Progression Informed Consent Form
  - If the subsequent scan continues to show progression, all therapy will be discontinued and the patient will be taken off study.

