#### **9.4.2 ANALYSIS OF THE PRIMARY EFFICACY HYPOTHESIS & STOPPING CRITERIA**

The one-sided proportion test will be conducted for ORR against the null hypothesis that the ORR is less than or equal to 3%, with significance level of 0.05. The cumulative frequency, estimated proportion, and the exact 95% confidence intervals will be reported. A sample size of 48 achieves 87% power if the ORR is 15% using a one-sided exact test with a target significance level of 0.05. These results assume that the ORR of the historical control is 3%.

For  $\alpha = 0.025$  (1-sided) and power of 87%, MinMax design supports stopping enrollment for futility as noted if there are no responses (partial response or complete response as defined in the protocol) in first 24 subjects. Otherwise, full study enrollment will proceed as planned. Using a Simon-like 2-stage design, ORR will be determined based on the first 24 evaluable patients (including patients in both Stage 1 and Stage 2). If there are no responses (partial response or complete response as defined in the protocol) in the first 24 evaluable patients, then study enrollment will be stopped for futility. If there is at least one response (partial response or complete response as defined in the protocol) in the first 24 evaluable patients then full study enrollment will proceed as planned. If there are no responses (partial response or complete response as defined in the protocol) in the first 23 evaluable patients then enrollment will be temporarily paused to allow response evaluation of the 24th evaluable patient after up to 15 total weeks (ie 5 total cycles) of study therapy. If the 24th patient has response (partial response or complete response as defined in the protocol) then then full study enrollment will proceed as planned. If the 24th patient does not have a response (partial response or complete response as defined in the protocol) then the study will be stopped for futility. See Section 9.4.2 for statistical considerations.

---

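### The futility rule contradicts itself: if one of patients 1-23 first responds during the pause, one sentence says proceed and the next says stop

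*Protocol*

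**What the plan says.** The interim decision is described in section 4.1.1 and repeated in section 9.4.2; section 9.4.6 plans no other interim efficacy analysis.

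- **Basis.** "ORR will be determined based on the first 24 evaluable patients (including patients in both Stage 1 and Stage 2").
- **Stop.** With no response "in the first 24 evaluable patients, then study enrollment will be stopped for futility".
- **Proceed.** With at least one response "in the first 24 evaluable patients then full study enrollment will proceed as planned". The notes to the study schema (section 1.2 and again in section 4.1) give the same rule: stop at none, and "Otherwise, full study enrollment will continue as planned".
- **Pause.** With no response "in the first 23 evaluable patients then enrollment will be temporarily paused to allow response evaluation of the 24th evaluable patient", who is read "after up to 15 total weeks (ie 5 total cycles) of study therapy".
- **End of the pause.** If patient 24 responds, enrollment goes on. Otherwise: "If the 24th patient does not have a response (partial response or complete response as defined in the protocol) then the study will be stopped".

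On timing, section 8.1 says: "Evaluation of tumor response conforming to RECIST v1.1 and iRECIST must be documented every 9 weeks", with a margin of 5 days and a calendar anchored on Cycle 1 Day 1. Appendix 2 (section 12.2) counts a patient as evaluable for response after at least one cycle and one disease re-evaluation, or on earlier objective progression.

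**The concern.** The stop and proceed sentences count responses in all 24 patients. The last sentence of the pause branch counts patient 24 only. The two agree as long as patients 1-23 stay without a response. They give opposite instructions when one of those patients first responds after the pause has begun, because the protocol nowhere says whether the count of zero in 23 is fixed at that moment or read again at the end.

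The branch is the later and more specific text, so a team could follow it in good faith and close a trial that has a documented response among its first 24 patients. That would break the design rule on which the interim look rests. The branch also speaks of stopping the study, where the design rule speaks of stopping enrollment.

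**Working it through.** **1. The plan's own figures.** Inputs from section 9.4.2: N = 48, null ORR 3%, target ORR 15%, one-sided exact test, stated power 87%.

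- Success at 5 or more of 48: alpha = P(X ≥ 5 | 48, 0.03) = 0.0143; power = P(X ≥ 5 | 48, 0.15) = 0.866. This reproduces the 87%.
- With the stop at 0/24 added: alpha 0.0140, power 0.860.
- P(stop) under 0/24 is 0.97^24 = 48.1% at ORR 3% and 0.85^24 = 2.0% at ORR 15%.

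The 0/24 rule is therefore sound if all 24 patients are counted.

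**2. Who can still respond when the pause starts.** Section 5.5 plans about 5 sites at 1 patient per site per month, so 5 / 30.4 = 0.164 patients a day. Take the pause to start at patient 23's week-9 scan (day 63).

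- Patients who entered in the 63 days before patient 23: 63 × 0.164 = 10.3. With patient 23 that is about 11 of 23 who have not reached week 18 (day 126).
- Patient 24 enters about 30.4 / 5 = 6 days after patient 23 on average (median about 4 days) and is read at day 105. The pause lasts 105 − 63 = 42 days plus that gap: median about 46 days, or 6.6 weeks.
- A week-18 scan falls inside the pause if the patient entered at least 126 − 105 = 21 days before patient 24, or about 15 days before patient 23. That leaves (63 − 15) × 0.164 = about 8 of the 11.

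**3. Size of the conflict.** Simulation at ORR 15%, Poisson entry at 5 a month, each response first seen at week 9 or week 18. The share first seen at week 18 is an assumption. The pause starts if patients 1-23 show no response at patient 23's week-9 scan. The literal branch then reads patient 24 alone, up to day 105.

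| Share first seen at week 18 | P(stop), literal branch | of which a response in patients 1-23 is already recorded (points) |
|---|---|---|
| 0% | 2.0% | 0 |
| 10% | 2.5% | 0.3 |
| 20% | 3.1% | 0.8 |
| 30% | 3.9% | 1.3 |
| 40% | 4.9% | 2.1 |
| 50% | 5.9% | 3.0 |

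Counting all 24 patients at the same day-105 cut-off gives about 2.2% at a 10% late share and 2.4-3.0% at 20-50%. At a late share of 50%, for example, 5.9 − 3.0 is about 3.0% after rounding.

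**4. Patient 24's window.** Scheduled scans fall on days 58-68 (week 9) and days 121-131 (week 18). Fifteen weeks is day 105, so the window holds one scheduled scan.

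**The case against.** The strongest reply is that there is no real conflict. The proceed sentence covers all 24 patients without exception, and the schema notes say the same. The branch is conditional on no response in the first 23. If one appears, the condition no longer holds and enrollment proceeds. This is a fair reading and probably the intended one. It does not remove the problem, because the text does not say that the condition is read again, and the sentence that governs the end of the pause names only patient 24.

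It is also fair that the effect is small, that it rests on an assumed late share, and that part of the excess over 2.0% comes from reading at a fixed date. No time-limited look can count every eventual response.

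Four stronger readings are tempting and are not supported:

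- **That the branch replaces the 0/24 rule.** Nothing says so; the 0/24 rule stands in both sections and in the schema notes.
- **That a response recorded before the pause could be ignored.** Such a response prevents the pause.
- **That the short window for patient 24 causes responses in patients 1-23 to be overlooked.** The two are unrelated; the window affects only how patient 24 is read.
- **That the pause lasts 15 weeks.** The 15 weeks are patient 24's time on therapy, most of which has passed when the pause starts under the timing above.

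**Conclusion.** The point holds as a contradiction in the stop rule for one situation: a first response in patients 1-23 that appears during the pause. The protocol then says both proceed and stop.

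The literal branch raises the false-stop probability at ORR 15% from 2.0% to about 2.5-5.9%, and 0.3-3.0 points of that are stops with a response already recorded in patients 1-23. This assumes 5 patients a month, scans at weeks 9 and 18, response counted when first seen, patient 24 read at week 15, and 10-50% of responses first seen at week 18. With no late responses the two rules give the same answer. Slower accrual leaves fewer patients open and makes the excess smaller.

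The absolute risk is a few points. It should still be corrected, because this is the only planned interim efficacy decision, it can end the trial, and the correction is wording only.

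**What to change.** In sections 4.1.1 and 9.4.2, replace the sentences that let patient 24 alone decide with:

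*At the end of patient 24's evaluation window, enrollment stops for futility only if none of the first 24 evaluable patients has a recorded response; a response in any of the 24 by that date means enrollment proceeds.*

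This keeps the 15-week cut-off, settles whether the study or its enrollment stops, and brings the stop probability at ORR 15% to about 2.2-3.0% over the same range. It costs an amendment of wording and has no real downside.

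Separately and optionally, the sponsor may align the read-out with patient 24's week-18 scan, since only the week-9 scan is scheduled within 15 weeks. That is a design choice and is not needed to remove the contradiction. It would lengthen the pause by about 18 − 15 = 3 weeks, in the roughly 2.4-6.4% of trials that pause if the ORR is 15% (late share 0-50%).

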#### **4.1.2 CRITERIA FOR CONTINUATION OF TREATMENT BEYOND RECIST V1.1- DEFINED PROGRESSION**

In all cohorts, at the time of RECIST v1.1-defined progression (i.e., iUPD), treatment is permitted to continue until the next assessment (at least 4 weeks but no longer than 8 weeks later) if the following criteria are met:

- Patient is clinically stable (An assignment of clinical stability requires that no worsening of performance status has occurred, that no clinically relevant increases in disease-related symptoms such as pain or dyspnea occur that are thought to be associated with disease progression (these symptoms are generally understood to mean a requirement for increased palliative intervention), and that no requirement for intensified management of disease-related symptoms exists, including increased analgesia, radiotherapy, or other palliative care.)
- Absence of tumor progression at critical anatomical sites (e.g., leptomeningeal disease) that cannot be managed by protocol-allowed medical interventions
- Patient and investigator agree to continue treatment

- Patient signs the Treatment Beyond Progression Informed Consent Form
- If the subsequent scan continues to show progression, all therapy will be discontinued and the patient will be taken off study.

At least 28 days and no more than 35 days after discontinuation of treatment, patients will return to undergo the listed activities in Schedule of Events (section 1.3, unless already completed in the last week, or last 6 weeks for response assessment). Patients continuing to experience toxicity at this point following discontinuation of treatment will continue to be followed at least every 4 weeks until resolution or determination, in the clinical judgment of the Investigator, that no further improvement is expected. If the patient has any concern and contacts the clinic, the patient will be seen in the clinic within 5 calendar days of the patient's contact with the clinic (assessments will be the same as the assessments performed at the Final Study/Treatment Discontinuation Visit). Overall survival information will be collected via telephone calls and/or clinic visits every 3 months  $\pm$  14 days (first call and/or clinic visit to occur 3 months following the Final Study/Treatment Discontinuation Visit) until death, withdrawal of consent, the patient is lost to follow-up, study termination by AGICC, or a maximum of 2 years from the Final Study/Treatment Discontinuation Visit.

## Study Schema

[figure not shown]

### 1. Dose Levels:

- Evorpaccept (ALX148) dose level (DL) 1: 15 mg/kg weekly; DL -1: 10 mg/kg weekly; DL -2: 5 mg/kg weekly
- Cetuximab DL 1: 250 mg/m^2 weekly; DL -1: 200 mg/m^2 weekly; DL -2: 150 mg/m^2 weekly
- Pembrolizumab DL 1: 200 mg every 3 weeks (no additional dose levels)

2. The desired mechanism of action of cetuximab is to augment phagocytosis via antibody-dependent cellular phagocytosis (ADCP) rather than to modulate the EGFR signaling pathway.

3. No more than 18 evaluable patients will be accrued in Stage 1. A single patient will be treated with evorpacept (ALX148), cetuximab, and pembrolizumab, followed by a 48-hour safety observation period prior to treating the next patient. A 48-hour safety observation period will be required between the start of treatment for patients in Stage 1. Additional patients may be enrolled at lower dose levels if at least 33% of patients experience a first-cycle dose limiting toxicity.
4. If a significant portion of patients in Stage 2 experience AEs meeting dose-limiting toxicity (DLT) criteria as defined in Section 4.1.5, then dose reduction(s) of evorpacept (ALX148) and/or cetuximab for subsequent patients can be considered in discussion with the Investigators and Medical Monitor.
5. A Simon-like 2-stage design will be used. If there are no responses (partial response or complete response) among the first 24 evaluable patients (including patients in both Stage 1 and Stage 2), study enrollment will be stopped for futility. Otherwise, full study enrollment will continue as planned.
6. Patients in Cohort A will provide a fresh pretreatment biopsy sample (before C1D1 but after screening) and an on-treatment biopsy sample at C3D1 ( $\pm 3$  days). While the acceptable window for the C3D1 biopsy is  $\pm 3$  days, it is preferred for the biopsy to occur following all treatments on C3D1. The date and time of the biopsies will be documented. In Cohort A, archival tissue may not be used in place of a fresh pre-treatment biopsy. Patients in Cohort B will not undergo any study-mandated biopsies. When available, archival tissue will also be obtained for analysis for patients in both Cohort A and Cohort B. For a subject in Cohort A, if the Investigator judges the risk for the pre- or on-treatment biopsy to be unacceptable in a research setting eg, based on complications during a previous procedure, use of blood thinning medications, or inaccessible tumor, or the patient refuses, a subject should not undergo the pre- or on-treatment biopsy and the patient will be allowed to enroll in or remain on the study. If a patient initially assigned to Cohort A is unable to undergo both the pretreatment and on-treatment biopsies due to medical reasons or patient refusal, an additional patient may be enrolled in Cohort A (to achieve N=23 patients who underwent pretreatment and on-treatment biopsies). Other than biopsies, there are no differences between Cohort A and Cohort B (both receive the same treatment and study events). Details for handling of these samples including processing, storage, and shipment will be provided in the Laboratory Manual.
7. The maximum duration of pembrolizumab is 35 cycles. There is no maximum duration of evorpacept (ALX148) or cetuximab.

